[figure not shown][figure not shown]

**PROTOCOL TITLE: MUTTON-HF (Medically Utilized Tailored Traditional food to Optimize Nutrition) in Heart Failure**

**Version Date 4/30/2025**

**Clinicaltrials.gov Registration: NCT06549699**

## **SECTION 1: RESEARCH PLAN**

### **Statement of Purpose:**

The American Indian and Alaska Native population has experienced significant cardiovascular health disparities compared with other racial and ethnic groups in the U.S. [1] Heart failure, in particular, causes significant morbidity and mortality in Navajo Nation. For many Navajo patients, similar to other American Indian populations, food insecurity is a major driver of health disparities. [2][3] In fact, qualitative data from our heart failure patient advisory committee have found that 89% of patients with heart failure believe nutrition insecurity is a major barrier to optimal health. Dietary factors are believed to be an important cause of hospitalizations in patients with heart failure and cardiovascular outcomes. There is increasing evidence that direct dietary support, such as produce prescription or provision of medically tailored meals may improve cardiovascular outcomes and disease-specific quality of life.[4][5] Furthermore, there has been an increased focus in Indigenous communities to reclaim traditional indigenous foods to improve health. However, more evidence of the benefit of traditional Indigenous foods for cardiovascular health is needed.

We, therefore, in discussion with community members and tribal partners at two Indian Health Service (IHS) sites in Navajo Nation, will implement and evaluate the effectiveness of a medically and Native-sourced culturally tailored meal delivery program to improve outcomes in heart failure in rural Navajo Nation. This study includes two phases, with a phase I pilot feasibility study, followed by phase II—a comparative effectiveness randomized controlled trial to compare the implementation of our medically and culturally tailored meal delivery program compared to usual care. Phase I outcomes included implementation outcomes such as feasibility and acceptability to inform phase II. The primary outcome for the trial in Phase II will be the proportion of patients who have a hospitalization or ER visit for any cause within 90 days post implementation period start date. Secondary outcomes will include: heart failure hospitalizations specifically, ER visits for volume overload specifically (ER visits for lower extremity edema, dyspnea, with clinical evaluation consistent with volume overload) within 90 days, Kansas City Cardiomyopathy Questionnaire clinical summary score at baseline and at 60 days; prescription adherence rates (% of filled prescriptions out of prescriptions made) for all medication as well as GDMT specifically at 60 days, weight at baseline (and BMI) at 60 days, and the following lab parameters and biomarkers at baseline and at 60 days: albumin, prealbumin, creatinine, NT-proBNP,

HbA1c, total cholesterol, LDL-C, HDL-C, Triglycerides, CRP, urine albumin:creatinine ratio. We will also collect measures of and measures of food insecurity, financial stress, Indigenous cultural connectiveness using the validated Cultural Connectedness Scale-California (CCS-CA), the Indigenous Nourishment Scale, as well as qualitative analyses of patients and local food suppliers to evaluate how this program strengthens local food systems. We will also evaluate food diaries and perform a survey at 90 days to evaluate for any sustainable change in diet and behavior post intervention. Semi-structured interviews will be performed of stakeholders including a subset of patients, primary care providers and food suppliers to assess implementation outcomes.

**Probable Duration of Project:** 24 months

**Research Plan:** We plan to conduct a randomized, comparative effectiveness design trial, with 1:1 randomization. This will be done at two IHS clinical sites in the Gallup Service Unit at Indian Health Service: Gallup Indian Medical Center (GIMC) and Tohatchi Health Clinic (THC), with the plan to expand to Fort Defiance Medical Center and/or Shiprock Medical Center if we are unable to enroll our target sample size.

**Study Population:** All patients 18 years of age or older, with diagnosis of heart failure based on ICD code I50\* with a hospitalization (any cause) in the last 12 months. Only patients with active prescription through IHS and engaged in care at our centers (clinical visit within last 12 months) will be included. We will exclude patients on hospice care or those residing in an acute care or skilled nursing facility, or any patient currently residing outside of the 50-mile IHS Gallup Service Unit catchment area.

**Subject Recruitment:** Eligible patients are identified through a query through iCARE, a EHR based data system through the IHS EHR. Patients with ICD10 diagnostic criteria for HF will be identified (ICD10\*). The inclusion criteria will be all adults  $\geq 18$  years, who have a prescription in the IHS system in the last 12 months and have had a clinical visit at GIMC or THC in the last 12 months, as well as a hospitalization (all-cause) in the last 12 months. Patients will be consented verbally either at the health center or verbally over the phone to enroll. If we have not met our 50% enrollment goal by 6 months, we will expand enrollment to another Navajo IHS site—Fort Defiance and/or Shiprock Medical Center, and enroll patients with ER visit (rather than just hospitalization) in the last 12 months.

**Enrollment:** All patients that meet eligibility criteria and consent to participate will be enrolled to receive meal delivery simultaneously: all enrolled patients will start receiving the intervention at the same starting time point,  $t=0$ . Patients randomized to usual care will also start the “intervention” of usual care at the time  $t=0$ , so that all patients will have outcome assessment on the same time schedule. For operation and logistical considerations, all baseline assessment (including consent, enrollment, baseline surveys and lab work) will occur in the enrollment period (-45 to 0 days prior to the intervention period). No clinical events will be included during the enrollment period as an outcome.

**Randomization:** Randomization in this study will occur at the level of the patient in a 1:1 fashion. Randomization will be stratified by sex, age ( $<65$  years,  $\geq 65$  years) and by left ventricular ejection fraction  $<50\%$  versus  $\geq 50\%$ . Patients living in the same household will be randomized to the same treatment assignment to avoid contamination.

**Intervention**

**- Phase I:**

## 1. A. Designing Culturally Relevant Medically Tailored Meals

We partnered with Tocabe, an Indigenous-run meal program, offering healthier and traditional foods, utilizing food from Native farmers and food producers.[6] Tocabe is a native-sourced and native-owned organization, which provides ready-made medically tailored meals to customers. In addition, they have extensive experience providing Indigenous and locally sourced foods direct to tribes. As part of Phase I and Phase II planning, we had local experts in Diné cuisine meet with our partners at Tocabe, to help develop a menu of culturally relevant meals and recipes. As part of this process, we determined key high priority Navajo food items, e.g. mutton, and recipes that are culturally important to include as part of our medically tailored meals. We designed different meal plans with a variety of options, all based on culturally relevant foods and recipes which will be incorporated as part of our medically tailored plan. Meals were designed to incorporate local and traditional Navajo foods. Meals were medically tailored to be consistent with sodium-restricted Dietary Approaches to Stop Hypertension as per American Heart Association recommendations.[6][7] Meals will be designed with cultural diet experts as well as registered dietitians to ensure meals are optimized medically and culturally. As much is feasible, we partnered with local Navajo farmers coalitions to locally source all ingredients and produce to strengthen local food systems and food sovereignty, and also to increase to increase accessibility of the meals and the likelihood of long-term adoption of recipes and meals after the intervention period.

## 1.B Supply Chain and Meal Delivery Logistics

As part of Phase I, we established and secured a supply chain for meals, and secured logistics for meal delivery, particularly for those living rurally on the reservation. Among a sample of n=22 HF patients, we found that 95% of patients had PO boxes (without a physical address/mailbox). Given this, we have partnered with the Gallup Food Pantry, and will have frozen meals prepared, packaged, and delivered to the Gallup Food Pantry in bulk as a central food hub, with subsequent patient distribution. Patients that live locally and are able to pick up meals will come pick up meals weekly. Those who are unable to pick up meals (or do not come for their meals), will have meals delivered weekly through various mechanisms (per patient preference) that were tested and deemed successful in our pilot trial. These include delivery to a minihub (Chapter House, Tohatchi Health Clinic) for pick-up, delivery by community health representative (CHR) or nurse, and peer delivery (pick up at food pantry and delivery by another participant living in same community for peer that is unable to pick up). For those without refrigeration, meals will be delivered to local chapter houses, and patients will pick up 3-day supply of meals in freezer boxes. In addition to refrigeration, we will also assess and address household infrastructure (e.g. ability to store and heat meals). We developed these logistical plans and evaluated them in our pilot feasibility trial, which has informed operationalizing our phase II comparativeness effectiveness trial.

[figure not shown]

## 1. C. Pilot Feasibility Trial

Prior to trial enrollment, we conducted a 6-month feasibility trial in which we enrolled a total of 20 patients, to test feasibility of home delivery of meals and obtain patient input on acceptability to optimize our larger scale trial. Our IHS study facilities have a catchment area of over a 50-mile radius. Of 20 patients enrolled, patient's locations of residence are shown in the map.

Given the geographic distance between patients, the rurality of locations, and lack of mailboxes or mailing addresses for many patients, we conducted a pilot feasibility study of 20 patients to ensure feasibility of patient delivery and acceptability of the medically and culturally tailored meals. Patients received 2 meals daily (14 meals weekly) for 4 weeks. Meals were prepared, packaged, and delivered in bulk to our central food hub (Gallup Food Pantry). From there, based on patient preference, a 1-week supply of meals was either picked up weekly by the patient or delivered by preferred patient mode of delivery (delivery to minihub, delivery by CHR, peer delivery). Patients also received 1 cooking class to learn how to make recipes from the meal plan, all incorporating locally available ingredients.

We assessed implementation outcomes including feasibility, acceptability, adoption, and fidelity of the intervention. Complete details on the pilot feasibility study protocol and outcomes are available online.[8][9]. Given implementation success as defined, we will proceed with phase II, with study design and outcomes informed by results of our pilot trial.[9]

## - Phase II: Comparativeness effectiveness trial of Medically and traditionally tailored meals for Heart Failure

We will conduct a comparativeness effectiveness trial to evaluate the impact of providing medically and culturally tailored Indigenous focused meals delivered to heart failure patients. Meals will be prepared, packaged, and delivered once weekly, with delivery mechanism based on community and patient preference. Two meals will be provided daily for 60 days. Along with the meals, patients will also receive recipe cards with each meal, as well as educational information regarding the meals, traditional food items included, and nutritional information, to educate on the health benefits of the food provided, as well some information regarding the traditional foods included and from where they were sourced. Additionally, patients will receive one cooking class conducted by a Diné Registered Dietician ([name]) to learn how to make a few key recipes from the meal plan, all utilizing locally available ingredients.

**Baseline Characteristics:** In addition to the American Heart Association sociodemographic core measures, we will also collect tribal affiliation, language, and in which local chapter/community patients reside.

**Endpoints:** The primary outcome for the trial will be the proportion of patients who have a hospitalization or ER visit for any cause within 90 days post intervention period (all patients will start the study at t=0 as described above). We will not include hospitalizations that occur electively for an elective procedure.

Secondary outcomes will include: heart failure hospitalizations specifically, ER visits for volume overload specifically (ER visits for lower extremity edema, dyspnea, with clinical evaluation consistent with volume overload), change in weight and body mass index at 60 days from baseline, Kansas City

Cardiomyopathy Score (and its components including summary score, physical limitation score, symptom frequency score, quality of life score and social limitation score)[10], and the following lab parameters and biomarkers at baseline and at 60 days: albumin, prealbumin, creatinine, NT-proBNP, HbA1c, Total cholesterol, LDL-C, HDL-C, Triglycerides, CRP, urine albumin:creatinine ratio. Lab work will be permitted to be collected 14 days before 60 days mark and up to 30 days after (from 46 days-90 days post intervention period).

*Additional secondary outcome measures:*

*Diet Quality*

- We will assess diet quality using the 10-item DSQ [11] with an addition question to assess traditional Diné food intake (*During the past month, how often did you eat traditional Diné foods (such as blue corn mush, steamed, roasted or dried corn, sumac berries, mutton, local varieties of squash or beans)*) at baseline and at the end of the intervention period.

*Food Security*

- We will evaluate baseline and 60-day rates of food insecurity utilizing the USDA Adult Food Security: Six Item short Form survey (USDA FSSM 6-Item).[12] At the 60-day evaluation, we will adapt the USDA FSSM 6-Item questionnaire to evaluate food insecurity within the last 2 (rather than 12 months).

*Indigenous Cultural Connectedness:*

- We will measure cultural connectedness utilizing a 6-question modified version of the validated Cultural Connectedness Scale-California (CCS-CA) at baseline and at 60 days.[13] This is a validated score, developed by Indigenous scholars to measure cultural connectiveness in Indigenous populations, and has been shown to correlate with physical health and be a social determinant of health.[14] This scale has previously been modified for use in Diné populations specifically by our group.

*Indigenous Nourishment Scale*

- We will evaluate the Indigenous Nourishment Scale (Measure A) [15], which is a scale developed through community-based methods in Indigenous communities to encompass multiple dimensions of nourishment. This scale offers an Indigenous framework to allow for health measurements rooted in Indigenous perspectives. We will evaluate Measure A of this scale at baseline and 60-days. We will score each question from 0 (never) to 6 (always) for a total score 0-54.

*Financial Stress*

- We will measure Financial Stress Scale at baseline and at 60 days using two questions:[16]

- How worried were you over the last 2 months about paying for housing (rent, mortgage, etc.)?
- How worried were you over the last 2 months about paying monthly bills?
  - All questions will be answered on a 4-point scale, where 1 = “not worried at all”, 2 = “not too worried”, 3 = “moderately worried”, and 4 = “very worried”

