#### *General Health Status:*

- We will evaluate patients' general health status using a single general health status question (would you say that in general your health is excellent, very good, good, fair, or poor) at baseline and post-intervention.

Outcomes determined by review of medical, hospital, and billing records, as well as patient surveys and semi-structured interviews. We will also extract medication at baseline and at 60 days to assess for changes in medical therapy. All patients will be provided a scale and blood pressure cuff for weight and blood pressure measurements, respectively. Patients will be instructed to take weights first thing in the morning (or pick a time-up front for all weight measurements for consistency). All patient-reported measures, including KCCQs and CCS-CA scores will be over the phone or in person per patient preference. Patients will come in for lab work at baseline and at 60 days. For patients who are unable to come with for lab work at 60 days (and within the window of 45-90 days), then we will have public health nurses provide outreach to collect blood work in the home. Patients will receive a text message (if they have a cell phone) or phone call on the landline (if no cell phone) to remind them to complete food diaries, weights, and other patient-reported measures in a timely manner. If patients are unable to come in for baseline lab work prior to intervention period, we will use completed lab work as baseline lab work if within 90 days 90 days of the intervention period. For those that have trouble completing written food diaries, we will collect this information verbally over the phone.

For subsequent planning purposes, we will also track costing data to determine the complete cost of the intervention and estimate total program costs (including all resources, even donated, involved in the implementation of the program, but not including research activities such as blood tests).

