Comparator: Those randomized to usual care will not receive any home delivery meals but will receive the recipes of healthy recipes that incorporate traditional local foods and educational booklet. They will also receive a gift bag for agreeing to participate in the study and a \$50 gift card upon completion of the study. Given ethical concerns about those not enrolled to receive the food is medicine intervention, after discussion with our community partners, we will provide 2 meals daily (14 meals weekly) for 4 weeks for all patients randomized to the control group after the study period (and outcome assessment) is complete if patients wish to receive meals and no safety concerns are identified.

Blinding of Intervention: Patients will be informed that they are enrolled in a program to receive medically and culturally tailored meals at home, and thus will not be blinded to their randomization status or participation in this trial. Providers will be not blinded to the intervention. Outcomes will be pulled from the EHR from study members, and those performing the analyses will be blinded to randomization status of the patient.

Enrollment Period: To allow time to coordinate the necessary operational and logistical infrastructure for meal delivery based on patient location/community and delivery mechanism, patients will be

consented and enrolled  $t=-45$  to  $t=-1$  days prior to the start of the intervention period ( $t=0$  for all patients). During this time, baseline assessment with surveys and lab work will take place. All patients will then start the study period (and outcome assessment period) at the same  $t=0$ . Any events that take place in the  $-45$  to  $-1$  days prior to the intervention period will not be included as an outcome. Summary of enrollment, intervention, and outcome assessment timeline is shown below.

[figure not shown]

Intervention Duration: The study team will implement the food intervention for 60 days.

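### Laboratory values counted as 60-day outcomes may be drawn up to day 90, a month after meals stop, which could attenuate the secondary biomarker differences

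*Protocol*

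**What the plan says.** The Phase II section fixes the exposure: "Two meals will be provided daily for 60 days". The Intervention Duration paragraph agrees: "The study team will implement the food intervention for 60 days".

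The Endpoints paragraph of the Phase II section lists among the secondary outcomes "the following lab parameters and biomarkers at baseline and at 60 days: albumin, prealbumin, creatinine, NT-proBNP" and further markers. It then sets the collection window: "Lab work will be permitted to be collected 14 days before 60 days mark and up to 30 days after", glossed as "from 46 days-90 days post intervention period".

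The outcome-collection paragraph under General Health Status says patients come in for blood work at baseline and at 60 days. For those who cannot attend at 60 days and "within the window of 45-90 days", it says "we will have public health nurses provide outreach to collect blood work in the home". It gives no day on which outreach starts.

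The Statistical Analysis section describes within-group laboratory changes as running to week 8. Elsewhere day 90 is a separate time point. Under Implementation Outcomes, the 90-day survey looks at diet after the intervention. Under Exploratory Outcomes, weight at 90 days is an additional measure distinct from weight at 60 days.

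**The concern.** The label on these outcomes (60 days, or week 8) describes patients at the end of the meal period. The window also admits patients who have been without the meals for up to 30 days, and it extends further on that side (30 days) than on the meal side (14 days). The protocol states no preference for a draw while meals are still being supplied.

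Under Comparator, control patients receive meals only after outcome assessment is complete. A late draw therefore compares former recipients with patients who have had no meals. If the effect on a marker fades after day 60, the observed difference is smaller than the end-of-intervention difference, and a null result could not be told apart from late sampling. Surveys and the main weight measure are scheduled at day 60, so one patient's symptoms and biomarkers could describe different exposure states. An analysis plan written later can model the draw date, but it cannot recover samples that were not taken while meals were running.

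**Working it through.** **The protocol's window.** Inputs: nominal day 60, minus 14, plus 30 (Endpoints paragraph).

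- 60 − 14 = 46 and 60 + 30 = 90, which reproduces the stated limits.
- Days are therefore counted from t=0. Read literally as days after the meals end, the gloss would give 60 + 46 = 106 to 60 + 90 = 150, which does not fit the rest of the same sentence.

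**Share of permitted days after meals stop.**

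- Days 46 to 90 inclusive: 90 − 46 + 1 = 45 days.
- Days 61 to 90: 30 days. 30/45 = 67%.
- With the opening day given under General Health Status (day 45): 30/46 = 65%. As an interval of 44 days: 30/44 = 68%.
- Week 8 is day 56, so a day-90 sample is 34 days from that label.

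**Illustrative attenuation.** The protocol gives no reversal rate and no distribution of draw dates; both are assumptions here. Suppose the full effect holds to day 60 and then decays exponentially with half-life h days, with late draws spread evenly over the 30 days. The mean retained effect among late draws is

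R = (1 − 2^(−30/h)) / (30 ln 2 / h).

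If a share f of draws is late, the loss is f × (1 − R).

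| Half-life h | R | Loss, f = 10% | Loss, f = 25% | Loss, f = 67% (even over window) |
|---|---|---|---|---|
| 7 days | 0.319 | 7% | 17% | 45% |
| 14 days | 0.521 | 5% | 12% | 32% |
| 28 days | 0.706 | 3% | 7% | 20% |

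**Effect on power, for scale only.** The protocol sets no target difference for laboratory outcomes. Take 204/2 = 102 per arm with complete data, and a difference that would have 80% power at two-sided 0.05: (1.96 + 0.84) × √(2/102) = 0.39 SD. With a fraction k of the effect retained, power is about Φ(2.80k − 1.96).

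- k = 0.90: 71%
- k = 0.75: 56%
- At f = 25%, k = 0.83, 0.88 and 0.93 for half-lives of 7, 14 and 28 days, giving about 64%, 69% and 74%.

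The primary outcome is hospitalization or ER visit within 90 days and does not use laboratory draws, so nothing above bears on it or on its sample size.

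**The case against.** The strongest reply is that the window is a tolerance around a day-60 target and not a plan to sample late. Patients are scheduled at 60 days, and the In-Kind Funding section provides navigators and nurses to call them about blood work. All patients share one t=0, so about 200 draws fall due together across a rural catchment of more than 50 miles, and a generous window is a sensible way to avoid missing data. Meals are also only part of the package. Recipe cards, education and a cooking class are intended to outlast the meals, so effects may persist. A window that closes on day 90 also ends with the primary outcome.

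Most of this stands, and it rules out several stronger readings that a reader might infer:

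- **That two-thirds of samples will be off meals.** The 67% is a share of permitted calendar days. The share of patients drawn late may be far smaller, and the 20% to 45% losses in the last column need draws spread evenly over the window, which nothing in the protocol supports.
- **That home draws will cluster near day 90.** The outreach sentence gives no start day and allows a visit at any point in the window.
- **That timing will differ by arm.** The window, reminders and outreach are not arm-specific. Later draws in controls are conceivable but undocumented.
- **That dilution is established.** It requires effects to fade. It would be small for slowly changing markers such as HbA1c, or if the change in diet persists.
- **That the window should simply be cut shortly after day 60.** This would trade possible attenuation for selective loss of the patients who are hardest to reach. It would also remove them from the per-protocol cohort, which requires the 60-day laboratory parameters.

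The reply does not remove the mismatch itself. The protocol treats day 90 as a post-intervention state for weight and diet, yet lets a day-90 blood sample stand as the 60-day value. It also expresses no preference for sampling before the meals end.

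**Conclusion.** The point holds as a possible, avoidable attenuation of secondary outcomes. What the text establishes is that meals end at day 60, that laboratory values labelled 60 days (or week 8) may come from as late as day 90, that 30 of 45 permitted days follow the last meal, and that the opening day is given as 46 in one place and 45 in another. The size of any bias is unknown. With 25% late draws and half-lives of 28 to 7 days it would be about 7% to 17% of the effect; with 10% late draws, about 3% to 7%. These figures rest on assumed decay and assumed draw dates. The direction is towards no effect if benefits fade, and there is no such bias if they persist. The change is worth making because it is cheap and can only be made before the samples are taken.

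**What to change.** - State one window, with the same opening day, in the Endpoints paragraph and under General Health Status. Count it explicitly from t=0 and drop the wording that reads as days after the intervention.
- Set a target draw in the last two weeks of meals, about day 46 to day 60, in both arms.
- Start the reminders and nurse outreach already planned before day 60, in both arms, for anyone not yet drawn.
- Keep samples up to day 90, so that hard-to-reach patients are not lost from the intention-to-treat or per-protocol sets. Record the draw date.
- Pre-specify a supplementary analysis restricted to samples drawn by about day 60, with later samples labelled post-intervention. Alternatively, adjust for time off meals. Controls have no last meal, so use days past day 60 in both arms and let the arm difference vary with it. This can sit in the analysis plan.

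The cost is protocol wording, somewhat earlier and possibly more home outreach, and a smaller sample in the restricted analysis. That analysis selects on draw timing, which may relate to access to care, so it should support the all-samples analysis and not replace it.
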